#### 7.2.4. Product Accountability

An Investigational Product Accountability Record for GAMMAPLEX must be kept current by the clinical site and must contain:

- subject number and initials
- initials of the staff person dispensing the product
- dates and quantities of investigational product received with batch numbers
- dates and quantities of investigational product dispensed per subject with batch numbers
- dates and quantities of investigational product returned per subject with batch numbers

The Investigational Product Accountability Record must be completed to document receipt, dispensing, and running total of product at site and must be included in the shipment of all unused GAMMAPLEX to the central distributor. At the end of the study, the site must prepare a final Investigational Product Reconciliation Statement; this form will be collected by the monitor. These forms must be made available throughout the study for inspection by authorized representatives of the CRO, manufacturer/sponsor, and regulatory agencies. The investigator is responsible for the accountability of all used and unused product and supplies used in the study. Where available, affix the tear-off portion of the label to the source documentation or record in writing the batch number used for the infusion.

Any empty or partly used bottles of GAMMAPLEX must be retained at site until instruction is given that they may be disposed of. This will be after the monitor has inspected the accountability records. The monitor will then instruct site staff that bottles may be destroyed at site. A certificate of destruction must be completed to document this.

GAMMAPLEX must not be used outside of this protocol and must not be used for subjects who are not in this study.

### **7.3. Treatment Compliance**

GAMMAPLEX will be administered intravenously and only under medical supervision; therefore, compliance is not an issue in this study.

## **8. ASSESSMENT OF EFFICACY**

### **8.1. Primary Efficacy Variable**

The primary efficacy variable will be the percent of subjects attaining a platelet count of  $\geq 50 \times 10^9/L$  by Day 9 (the 7th day after completing the second infusion).

### **8.2. Secondary Efficacy Variables**

There will be 2 secondary efficacy variables:

- Duration of time for which the platelet count remains  $\geq 50 \times 10^9/L$  following the first treatment course of GAMMAPLEX
- Changes in the signs of any bleeding/hemorrhage up to Day 32 (see Appendix 1 for grading criteria)

## **9. ASSESSMENT OF SAFETY**

### **9.1. Safety Variables**

The variables used to assess safety will be the following:

- Adverse events
  - The number and percent of infusions with at least 1 AE that occurs during an infusion or within 72 hours after the infusion stops
  - Nature, severity, and frequency of AEs
  - Suspected unexpected serious adverse reactions (SUSARs)
- Vital signs
- Clinical laboratory tests and Direct Coombs' Test
- Transmission of viruses
- Physical examination

#### **9.1.1. Adverse Events**

For subjects who receive only 1 treatment course of GAMMAPLEX on Days 1 and 2, AEs will be documented from the date the informed consent form is signed until the End of Study visit on Day 90. For subjects who receive (an) additional course(s) of GAMMAPLEX, AEs will be documented from the date the informed consent form is signed until the End of Study visit which for this group of subjects is 90 days, approximately 3 months, after the first infusion of the last course of GAMMAPLEX. AEs will be reviewed and documented at each visit by examining the diary cards (for the first course of GAMMAPLEX up to Day 32) and by direct questioning of the subject.

The investigator will attempt to establish a diagnosis of the AE based on signs, symptoms, and/or other clinical information. It is the diagnosis that should be documented as the AE and not the individual symptoms.

#### **9.1.1.1. Definitions**

##### *Adverse Event*

An AE is any untoward medical occurrence not necessarily having a causal relationship to treatment. An AE can, therefore, be any unfavorable and unintended sign (including an abnormal laboratory finding), symptom, or disease (new or exacerbated) temporally associated with the use of a medicinal product, whether or not considered related to the medicinal product.

##### *Unexpected Adverse Event*

An AE is defined as unexpected if it and its severity are not indicated in the current Investigator's Brochure.

##### *Infusion-Related Adverse Events*

All AEs that occur from the start of the infusion until 72 hours after the infusion will be recorded as infusion-related, but will not necessarily be related to GAMMAPLEX per se.

##### *Clinical Laboratory and Other Adverse Events*

If a laboratory result is considered by the investigator to be clinically significant or have a clinically significant pathological change from baseline, it should be recorded as an AE.

Other abnormal results (e.g., x-rays, scans, physical examination findings) that worsen from baseline and/or are considered clinically significant should also be recorded as AEs.

The investigator will exercise his or her medical and scientific judgment in deciding whether an abnormal laboratory finding or other abnormal assessment is clinically significant.

##### *Serious Adverse Event*

An SAE is any untoward medical occurrence that, at any dose:

- Results in death
- Is life-threatening (places the subject at immediate risk of death)
- Requires inpatient hospitalization or prolongs existing hospitalization (does not include hospitalizations for elective procedures for pre-existing conditions that did not worsen from baseline)
- Results in persistent or significant disability/incapacity
- Is a congenital anomaly/birth defect
- Is an important medical event (event that may not be immediately life-threatening or result in death or hospitalization but may jeopardize the subject or may require medical or surgical intervention to prevent one of the other outcomes listed in the

above definition. Examples include: allergic bronchospasm requiring intensive treatment, blood dyscrasias or convulsions, and the development of drug dependency or drug abuse)

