| 
Duration of treatment: Each subject can receive up to 3, 2-day courses of GAMMAPLEX over a period of up to 90 days. The total duration of the study for each subject will be 90 days after the first infusion of the last course of GAMMAPLEX which could range from 90–180 days (approximately 3 to 6 months) depending on the number and timing of treatment courses received.
                                                                                                                                                                                                                                                                                                                                                                                                                                                                                                                                                                                                                                                                                                                                                                                                                                                                                                                                                                                                                                                                                                                                                                                                                                                                                                                                                                                                                                                                                                                                            |                                                                                                                       |

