##### *Pregnancy Test*

A urine-based HCG test will be done before the infusion with GAMMAPLEX on Day 1.

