### **6.3. Subject Withdrawal**

Subjects may be withdrawn from study for any of the following reasons:

1. The subject withdraws from the study on his/her own volition.
2. The subject develops Hepatitis B, Hepatitis C, or HIV as determined by a positive result on a test for HBsAg or on a NAT for HCV or HIV RNA, or the appropriate serological tests for these viruses.
3. The subject has a serious adverse event (SAE) while participating in the study and, at the discretion of the site investigator, is discontinued.
4. The subject becomes pregnant while participating in the study. Any subject that becomes pregnant while participating in the study will not receive any further infusions of GAMMAPLEX.
5. The investigator may withdraw subjects at anytime if they feel it is not in the subject's best interest to continue in the study.

If a subject's Day 1 blood sample results from the central laboratory (for Laboratory A, Laboratory B tests or for the other protocol required blood tests) are out of range, the subject will be withdrawn from the efficacy analysis only. These subjects will still be included in the safety analysis and will therefore continue to attend the follow-up visits. Subjects withdrawn from the efficacy analysis will not be eligible to receive any further courses of GAMMAPLEX.

If a subject receives any of the study product and withdraws, all of the assessments scheduled on Day 32 and the End of Study visit must be done, if possible. For subjects who received more than 1 course of GAMMAPLEX before withdrawal, every effort must be made to complete the assessments scheduled for the End of Study visit.

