### 9.1.1.4. Follow-Up of Adverse Events

All AEs will be followed until resolution, until the condition stabilizes, or until the subject is lost to follow-up. The investigator will ensure that follow-up includes any supplemental investigations that may be indicated to determine the nature and/or causality of the AE or SAE. The sponsor may require that the investigator perform or arrange for the conduct of additional investigations (not otherwise required per protocol) to determine the nature and/or causality of the AE or SAE.

Any subject that becomes pregnant during the study must be followed up to delivery.

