### 9.1.2. Submission of Serious Adverse Event Reports

When an SAE occurs, it is the responsibility of the investigator to review all documentation (e.g., hospital progress notes, diagnostic reports, laboratory assessments) relative to the event. The investigator will then be responsible for recording all relevant information on the appropriate AE CRF and SAE form. New information or corrected information will be recorded on a follow-up SAE report.

Any SAE that occurs at any time between the signing of the informed consent and 30 days after the last dose of study medication, regardless of the relationship to study medication, must be reported on the SAE CRF, and a copy of this form must be faxed to the drug safety manager, and in Argentina to ACTIVA-CRO, at the fax number(s) listed below within 24 hours of knowledge of the event:

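### A birth defect found in the required follow-up to delivery falls outside the stated 24-hour SAE submission period and, at term, outside the AE documentation period

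*Protocol*

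**What the plan says.** Four statements in the protocol bear on this.

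- **Definition.** Section 9.1.1.1, under Serious Adverse Event, lists "Is a congenital anomaly/birth defect" as a criterion.
- **Pregnancy follow-up.** Section 9.1.1.4 states: "Any subject that becomes pregnant during the study must be followed up to delivery".
- **AE documentation.** For subjects with one course, section 9.1.1 states: "AEs will be documented from the date the informed consent form is signed until the End of Study visit on Day 90". For subjects with repeat courses the end point is the End of Study visit, "90 days, approximately 3 months, after the first infusion of the last course of GAMMAPLEX".
- **SAE submission.** Section 9.1.2 sets the 24-hour duty for "Any SAE that occurs at any time between the signing of the informed consent and 30 days after the last dose of study medication", whatever the relationship to treatment.

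Three further statements fix the dates. On pregnancy testing, section 5.3.1.2 says "A urine-based HCG test will be done before the infusion with GAMMAPLEX on Day 1", in addition to the test at screening. Section 6.3 says "Any subject that becomes pregnant while participating in the study will not receive any further infusions of GAMMAPLEX". The synopsis gives the total duration per subject as a period "which could range from 90–180 days (approximately 3 to 6 months) depending on the number and timing of treatment courses received".

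**The concern.** The protocol names a birth defect as an SAE and orders the follow-up that would reveal it. It then states time limits that, for a term birth, close before the birth. Section 9.1.1.4 gives no form, recipient or deadline for the pregnancy outcome and extends neither limit. Section 10.4.1 counts subjects with AEs and SAEs, so an event outside both periods has no clearly stated way into those tables.

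What is at stake is whether a rare but serious outcome after exposure to a plasma product is reported promptly and consistently across sites. A site that applies the dates literally could conclude that it has no 24-hour duty. Efficacy is not involved.

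**Working it through.** This is date arithmetic. No power or sample-size formula applies.

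**Step 1. Reproduce the protocol's own figure.** End of Study = day of the first infusion of the last course + 90 days.
- One course: Day 90 (section 5.3.1.6).
- Last course starting at the latest on Day 90 (synopsis; sections 5.2 and 5.3): 90 + 90 = about Day 180.

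This matches the 90 to 180 days in the synopsis. The visit window of ±7 days (Tables 1 and 2) extends the limits to Day 97 and Day 187.

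**Step 2. End of the SAE submission period** = last dose + 30 days (section 9.1.2).
- One course: Day 2 + 30 = Day 32.
- Latest course, second infusion on Day 91: 91 + 30 = Day 121.

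**Step 3. Earliest delivery.** Delivery day = conception day + days from conception to delivery. The protocol gives neither term, so both are assumptions. I take conception no earlier than about Day -14, because the urine test must be negative on Day 1. I take 266 days to term, and vary it down to 154 days.
- Day -14 at term: -14 + 266 = Day 252.
- Day 1 at term: 1 + 266 = Day 267.

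**Step 4. Compare.** The table uses conception on Day -14, the case that gives the earliest birth, and includes the +7 days at End of Study. Entries are days from the limit to delivery; a negative entry means delivery before the limit.

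| Days to delivery | Delivery day | One course: SAE limit, Day 32 | One course: End of Study, Day 97 | Latest course: SAE limit, Day 121 | Latest course: End of Study, Day 187 |
|---|---|---|---|---|---|
| 266 | 252 | 220 | 155 | 131 | 65 |
| 245 | 231 | 199 | 134 | 110 | 44 |
| 182 | 168 | 136 | 71 | 47 | -19 |
| 154 | 140 | 108 | 43 | 19 | -47 |

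Without the +7 days, the term birth is 252 - 90 = 162 days after the one-course End of Study and 252 - 180 = 72 days after the latest one. Later conception moves every delivery later. Conception on Day 1 with a term birth gives 267 - 32 = 235 and 267 - 121 = 146 days after the two SAE limits.

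**Step 5. Is the latest-course column realistic?** Known pregnancy stops further infusions, which normally keeps the limits early. Table 2 lists no pregnancy test before a repeat course, so an undetected early pregnancy at a later course cannot be ruled out. I therefore keep this column as the bound most favourable to the protocol.

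**Result.** A birth at or near term (245 to 266 days) falls after both limits in every case. A very early birth (154 to 182 days) falls after the SAE limit in every case, but can precede End of Study when there was a late repeat course.

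**Step 6. Would a longer SAE period solve it?** Extending submission to the End of Study visit would still stop at Day 187 at the latest, before a birth on Day 231 or Day 252.

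**The case against.** A reader might infer that such a defect is neither reported nor counted, or that no case could ever be captured. The protocol does not support that, for these reasons.

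- **General recording duty.** Section 9.1.2 opens with a duty that has no time limit: when an SAE occurs, the investigator reviews the documentation and completes the AE page and the SAE form. The 30-day sentence governs the mandatory fax within 24 hours and does not forbid later reports. This stands, so one cannot say that no form applies.
- **SUSAR route.** Section 9.1.1.1 makes related, unexpected and serious events subject to expedited reporting without a time limit, and section 9.1 lists SUSARs as a safety variable. This stands, but only for defects judged both related and unexpected. The duty in section 9.1.2 applies whatever the relationship.
- **Other documents.** Section 9.1.3 refers to local requirements and leaves procedural detail to an SAE Management Plan that is not shown. That plan may cover pregnancy outcomes, so their absence cannot be established here. The cut-off itself, however, is stated in the protocol.
- **Intent.** Follow-up to delivery stands under the heading on AE follow-up, which suggests that the outcome is meant to be recorded. That supports stating it; it does not supply a deadline or recipient.
- **Date of occurrence.** A defect might be held to occur before birth, and one detected prenatally within a period would be captured. Dating it before birth does not close the gap: in a one-course subject who conceives after Day 32 and before Day 90, it would still arise after the SAE limit.
- **Rarity.** The planned minimum is 31 evaluable subjects, pregnancy is excluded at entry and contraception is required. This stands and limits the weight of the point.

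**Conclusion.** The point holds in a limited form. Followed literally, the stated cut-offs exclude a birth defect found at a term delivery from the mandatory 24-hour submission and from AE documentation, although the protocol defines it as an SAE and orders the follow-up that would detect it. At term the gap is at least 220 days beyond the SAE limit after one course and 131 days beyond the latest possible one. It is at least 162 and 72 days beyond the corresponding nominal End of Study dates.

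These figures rest on conception no earlier than about Day -14 and 266 days to term. The conclusion is unchanged at 245 days. It weakens only for a very early delivery after a late repeat course, which may fall within AE documentation but still misses the SAE limit.

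The defect lies in how sections 9.1.1, 9.1.1.1, 9.1.1.4 and 9.1.2 fit together. The SAE criterion itself is not wrong. The change should be made because it improves safety reporting at almost no cost. Few or no cases are expected, and neither the primary analysis nor any efficacy conclusion is affected.

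**What to change.** Reconcile the four sections. State in section 9.1.2, with a cross-reference in 9.1.1.4, that a congenital anomaly or birth defect found during follow-up to delivery is recorded and submitted as an SAE within 24 hours of knowledge, regardless of the time since the last dose or the End of Study visit. State also that such a case is included with the reported SAEs (section 10.4.1).

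The cost is a sentence or two. No visit is added, because follow-up to delivery is already required. The one drawback is that a case arising after the final report may need an addendum.

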#### *Suspected Unexpected Serious Adverse Events*

All AEs judged to be related to GAMMAPLEX that are both unexpected and serious (SUSARs) are subject to expedited reporting in the U.K. BPL will be responsible for reporting these to the concerned competent authorities.

#### **9.1.1.2. Assessment of Severity**

The investigator will make an assessment of severity for each AE and SAE reported during the study. Severity refers to the grading of adverse events to assess the severity of symptoms as evaluated by the investigator or as experienced by the subject. The severity grading is independent of seriousness; in other words, a severe event is not necessarily serious.

#### *AEs Occurring During the Infusion and up to 60 minutes from the End of Infusion*

The severity of AEs that occur during or less than 60 min after an infusion will be graded according to the criteria in Table 4.

#### *AEs Occurring Later than 60 minutes After the End of Infusion*

The severity of AEs that occur more than 60 min after the end of an infusion will be graded as follows:

- **Mild:** Event resolved spontaneously or no treatment was necessary beyond administration of non-prescription drugs.
- **Moderate:** Event required use of prescription drugs and produced no sequelae.
- **Severe:** Event produced sequelae or required a visit to health care professional.

**Table 4 Criteria for Grading Severity of Infusion-Related Adverse Eventsa that Occur During Infusion or up to 60 minutes from the End of Infusion**

| TYPE OF EVENT
Sign/Symptom                                                                                                                                     | Mild                                                   | Moderate                                                                                                     | Severe                                                                                                                                        |
|-------------------------------------------------------------------------------------------------------------------------------------------------------------------|--------------------------------------------------------|--------------------------------------------------------------------------------------------------------------|-----------------------------------------------------------------------------------------------------------------------------------------------|
| CARDIOVASCULAR                                                                                                                                             |                                                        |                                                                                                              |                                                                                                                                               |
| Tachycardia                                                                                                                                                       | HR = 1.2 to 1.4x baseline                              | HR = 1.41 to 1.6x baseline                                                                                   | HR > 1.6 x baseline                                                                                                                           |
| Arrhythmia                                                                                                                                                        | Occasional, asymptomatic
(not-present pre-infusion) | < 1 per minute, and
asymptomatic                                                                          | > 1 per minute, or
symptomatic                                                                                                             |
| Hypotension (% fall in
systolic or diastolic blood
pressure in mmHg (from
either pre-infusion
measurement, whichever is
lower – see Section 9.2.   | 10 to 15% b                                 | 16 to 25% b                                                                                       | > 25% b                                                                                                                            |
| Hypertension (% rise in
systolic or diastolic blood
pressure in mmHg (from
either pre-infusion
measurement, whichever is
higher – see Section 9.2. | 20 to 25% b                                 | 26 to 30% b                                                                                       | > 30% b                                                                                                                            |
| ALLERGIC                                                                                                                                                   | Pruritus without rash                                  | Pruritic rash; tachypnea
1.3 to 2 x the higher
baseline, chest tightness
suggestive of bronchospasm | Urticaria; tachypnea > 2 x
the higher baseline,
bronchospasm,
laryngospasm, angioedema,
circulatory shock (severe
hypotension) |
| SYSTEMIC                                                                                                                                                   |                                                        |                                                                                                              |                                                                                                                                               |
| Fever °F
(°C)                                                                                                                                                  | 99 to 101.2
(37.7 to 38.4)                          | 101.3 to 104
(38.5 to 40.0)                                                                               | >104
(40)                                                                                                                                  |
| Chills                                                                                                                                                            | Feels cold, slight shivering                           | Intermittent shaking                                                                                         | Continuous shaking, cold
and clammy skin                                                                                                   |
| Headache                                                                                                                                                          | Discomfort, but does not
require medication         | Responds to non-narcotic
analgesia                                                                        | Requires narcotic analgesia
or persistently recurrent
despite treatment                                                                 |
| Other pain                                                                                                                                                        | Discomfort, but does not
require medication         | Pain requiring non-
prescription medication.                                                              | Pain requiring prescription
and/or narcotic medication                                                                                     |
| Nausea                                                                                                                                                            | Discomfort, but does not
require medication         | Can take fluids without
antiemetic medication                                                             | Little or no oral intake
and/or requires antiemetic
medication                                                                          |
| Vomiting                                                                                                                                                          | 1 episode                                              | 2 to 3 episodes                                                                                              | > 3 episodes                                                                                                                                  |

a This table applies to AEs associated with an infusion that occur during an infusion and/or up to 60 minutes after an infusion. The infusion rate at which the AE is observed will be recorded.

b If not accompanied by an increase in heart rate and subject is assessed as being comfortable or sleeping, blood pressure changes of this magnitude may be classified by the investigator as physiologic and not considered an AE.

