##### *Vital Signs*

Vital signs assessed by qualified personnel will be entered on the CRF. The vital signs to be observed will be diastolic and systolic blood pressure (mmHg), pulse rate (beats/min), respiration rate (breaths/min), and oral temperature (°C). The subject must be in the same position each time vital signs are obtained. The vital signs are also a safety variable (see Section 9.2.).

*Blood Samples for Laboratory Tests*

Blood samples will be obtained for Laboratory A and Laboratory B (Clinical Laboratory tests are a safety variable, see Section 9.3). If a subject is otherwise eligible, but the platelet count is greater than  $20 \times 10^9/L$ , the subject will not be enrolled. If at a subsequent visit (within 6 months of the screening visit) the subject's clinical condition suggests to the investigator that their platelet count may have dropped, the subject may have their platelet count re-measured by the local laboratory. If the platelet count is  $\leq 20 \times 10^9/L$ , the general health of the subject has not significantly changed, and no changes in concomitant medications or treatment have occurred which would violate the inclusion criteria, then safety blood samples should be measured by the local laboratory e.g. CBC, LFTs, serum Creatinine/BUN. If these all meet the entry criteria then the subject can be considered as eligible, and can be immediately enrolled in the study.

*Other Blood Samples*

The following additional samples will be collected:

- Serum for IgG, IgA, and IgM levels
- A reserve sample (see Section 9.3.1)
- A sample for a Direct Coombs' test (see Section 9.3.2).
- NAT for HCV, HIV and Parvovirus B19
- Serology for HIV1 and HIV2, HCV, HBsAg
- Blood typing (A, B, O, Rh(D)+/-)

*Urinalysis*

A urinalysis with microscopic examination will be done as a part of this visit.

*Assessment for Bleeding/Hemorrhage*

The subject will be assessed for bleeding and hemorrhage; this will be graded as detailed in Appendix 1 and recorded on the subject's CRF.

*Concomitant medications*

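### Section 9.1.1.2 contradicts itself twice on AE severity: the lower Mild fever limit differs between °F and °C, and the grades for events after 60 minutes overlap with no tie-break

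*Protocol*

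**What the plan says.** Protocol Section 9.1.1.2 makes grading a site task: "The investigator will make an assessment of severity for each AE and SAE reported during the study". It then gives two scales.

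- **During infusion and up to 60 minutes after it (Table 4).** Fever limits are printed in °F with °C in brackets. Mild is "99 to 101.2 (37.7 to 38.4" and Moderate is "101.3 to 104 (38.5 to 40.0"; Severe is above 104°F (40°C). The vital-signs paragraph of Section 5.3.1.1 has temperature taken as "oral temperature (°C", so the recorded unit is Celsius.
- **More than 60 minutes after infusion.** The lowest grade, Mild, is worded as "Event resolved spontaneously or no treatment was necessary beyond administration of non-prescription drugs". One step up, the Moderate grade joins two conditions that must both hold: "Event required use of prescription drugs and produced no sequelae". For the top grade, Severe, either of two conditions is enough: "Event produced sequelae or required a visit to health care professional".

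Nothing in Section 9.1.1.2 says which temperature scale governs, or which grade applies when an event meets two definitions. Section 9.1 names AE severity among the safety variables, and Section 10.4.1 has it listed.

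**The concern.** A severity scale should give each event one grade. Here a low fever can be graded or not depending on the column read, and a late event can satisfy two definitions at once.

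The late-event scale matters more because it covers most of the observation time. Table 4 stops 60 minutes after an infusion. AE collection runs to the End of Study visit, 90 days after the first infusion of the last course (Section 9.1.1). Even the infusion-related window in Section 9.1.1.1 extends to 72 hours.

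Severity also enters the definition of an unexpected AE in Section 9.1.1.1, which compares an event and its severity with the Investigator's Brochure. An event with two defensible grades could therefore have two answers on expectedness. Because the grade is assigned at site, an analysis plan cannot cleanly repair it afterwards. The study has one arm and a minimum of 31 evaluable subjects (Section 5.2), so no concurrent arm shares the grading noise.

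**Working it through.** **Fever limits.** Inputs are the limits in the fever row of Table 4. The conversion is °C = (°F − 32) × 5/9, compared at the table's precision of 0.1.

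| Printed °F | Calculation | Result °C | Printed °C | Agrees |
|---|---|---|---|---|
| 99 | 67 × 5/9 | 37.22 | 37.7 | no |
| 101.2 | 69.2 × 5/9 | 38.44 | 38.4 | yes |
| 101.3 | 69.3 × 5/9 | 38.50 | 38.5 | yes |
| 104 | 72 × 5/9 | 40.00 | 40.0 | yes |

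In reverse, 37.7 × 9/5 + 32 = 99.86°F. At the lower Mild limit the scales differ by 37.70 − 37.22 = 0.48°C, or 99.86 − 99 = 0.86°F. The other three limits agree, so this is an isolated error and not a rounding convention.

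The affected band: 99.7°F is 67.7 × 5/9 = 37.61, or 37.6°C, which is Mild in °F and ungraded in °C. 99.8°F is 67.8 × 5/9 = 37.67, which rounds to 37.7°C and is Mild on both scales. The band is therefore about 37.2 to 37.6°C, or 99.0 to 99.7°F.

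The infusion-rate reduction in Section 7.2.3 is triggered by Moderate or Severe events as graded in Table 4. The fever limits for those grades convert correctly, so this error does not touch the trigger.

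**Late-event grades.** Each event is described by three yes/no features: prescription drug needed, sequelae, and visit to a health care professional required. For this table, assume that any treatment is by drugs. An event without a prescription drug then meets the second limb of the Mild definition.

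| Prescription drug | Sequelae | Required visit | Grades met |
|---|---|---|---|
| no | no | no | Mild |
| no | no | yes | Mild and Severe |
| no | yes | no | Mild and Severe |
| no | yes | yes | Mild and Severe |
| yes | no | no | Moderate |
| yes | no | yes | Moderate and Severe |
| yes | yes | no | Severe |
| yes | yes | yes | Severe |

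Four of the eight combinations meet two grades: one Moderate/Severe and three Mild/Severe. These are counts of combinations, not of expected events. The Mild definition's first limb, spontaneous resolution, would add further overlaps if an event could both resolve spontaneously and need a prescription drug. That pairing is arguable and is left out.

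**Can the overlap be removed by deleting the visit clause alone?** No. That settles the two rows in which a required visit is the only ground for Severe. The two rows without a prescription drug but with sequelae still meet both Mild and Severe.

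**The case against.** The case for treating this as minor has several sound parts.

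- **Fever.** Temperature is recorded in °C, so the Celsius limit may govern in practice. Sections 5.3.1.2 and 9.2 require each vital-sign change to be judged clinically relevant before it is listed as an AE, so a reading of 37.4°C need not become an event at all. Table 4 applies only until 60 minutes after infusion, and only the lower Mild limit is wrong.
- **Late events.** Severity is stated to be independent of seriousness, and SAE reporting under Section 9.1.2 does not depend on grade. The rate-reduction rule refers to Table 4, not to the late scale. The AE summary table in Section 10.4.1 has no row by grade.

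All of this stands and limits the consequences. It does not remove either contradiction.

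Three stronger readings are tempting, but the protocol does not support them.

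- A reader might infer that planned severity tables will be unreliable. The protocol promises a listing and names no severity table.
- A reader might infer a site effect, with °F sites reporting more fever than °C sites. No section says that any site grades in °F.
- A reader might infer that Moderate nearly empties into Severe, because a prescription usually needs a visit. The protocol says nothing of the kind. Severe refers to a visit that the event required, and subjects already attend on Days 3, 5, 9, 14, 21 and 32. A prescription written at a scheduled visit need not count.

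**Conclusion.** Both contradictions are confirmed from the protocol's own text.

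The fever error is certain and narrow: 0.48°C (0.86°F) at one limit, deciding only whether a reading of about 37.2 to 37.6°C is Mild or ungraded. Its practical effect may be small, because the recorded unit is °C and clinical relevance is assessed first.

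The late-event overlap is the more important half. It lets one event be Moderate or Severe, or Mild or Severe, with no rule to choose between them. Late severity grades are therefore not reproducible. How many events this affects cannot be derived from the protocol, which gives no expected rate of prescriptions, required visits or sequelae. Any effect on expectedness depends on the Investigator's Brochure, which is not at hand.

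Neither point touches the primary efficacy analysis, the sample size or the Moderate-or-Severe fever limits. The protocol should be corrected because severity is a named safety variable and the change is cheap, but the study's main conclusion does not depend on it.

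**What to change.** 1. **Fever row of Table 4.** Reconcile the lower Mild limit so that °F and °C state the same temperature. The protocol does not show which was meant, so the sponsor must choose. State that the grade is taken from the recorded °C value.
2. **Late-event scale.** Make the three grades mutually exclusive, either by reconciling all three definitions or by adding one rule, for example to assign the highest grade whose criteria are met. Under that rule all four double-graded rows above become Severe, including an event without prescription drugs or sequelae that required a visit. If the sponsor does not intend that, the definitions need rewriting. Deleting the visit clause by itself is not enough.
3. **Events already graded.** Re-review late events once under the settled rule and keep the initial grade on record. Fever grades can be checked against the recorded temperatures, although clinical relevance remains the investigator's judgement.

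The cost is protocol wording, a note in the CRF guidance and that single re-review. No new data are needed for the fever correction. Replacing the whole scale with CTCAE is not needed: Appendix 1 reproduces only its bleeding terms, and changing scales after enrollment has begun would create a new inconsistency.
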